## Background

In order to ensure their survival, preterm infants need to receive intensive care and therefore necessarily undergo repeated episodes of stress from therapeutic procedures. Converging evidence from animal and preterm infant studies suggests that chronic exposure to stress may alter brain development and may contribute directly and indirectly to the developmental impairments found later in this population.

For preterm infants, severe pain, such as post-operative pain, is controlled with pharmacological agents, while stress associated with minor procedures, such as suctioning or heel lance, is managed with non-pharmacological interventions such as sweet solutions given orally (e.g. glucose or sucrose) and facilitated tucking. These interventions need to be given prophylactically in order to be effective, have few associated adverse effects and are readily available. Importantly, new research indicates that sweetening agents may be most effective acting as sedatives (rather than analgesics), which makes them useful for comforting infants during stressful procedures which do not break the skin, especially when other modalities such as full maternal holding, etc. cannot be employed (i.e. during an ultrasound procedure).

The practice of targeted neonatal echocardiography (tn-ECHO) is rising in the intensive care unit for rapid, serial cardiac bedside assessment of cardiovascular function and response to therapy in the NICU and as an adjunct to evaluations normally performed by a Pediatric Cardiologist. Neonatologists use tn-ECHO to gain information about cardiac function, pulmonary pressures, and in common neonatal conditions such as persistent ductus arteriosus, as an extension of their clinical exams to improve clinical decision-making.

A standard tn-ECHO can take up to ½ hour to complete depending on compliance of the infant. In several NICUs across Europe and the USA, it has become common practice to soothe the infants with non-pharmacological interventions and, at times, with glucose water and facilitated tucking, *although evidence directly supporting this practice is absent, and the effectiveness of these types of interventions has not been formally studied.* Importantly, these interventions are thought to be useful not only to comfort the infant, but also to minimize infants' movement which may significantly decrease the amount of time required to complete the tn-ECHO. Increased infant movements during the procedure may even alter the hemodynamic profile of the heart complicating interpretation of the data.

This study aims to exploit this potential sedative effect of glucose and calming effects of facilitated tucking for managing minor procedural stress. Here we will determine whether the use of 25% glucose water with or without facilitated tucking reduces stress and performance time during tn-ECHOs in infants in the NICU.

## Purpose & Objective

Primary Objective: To compare the effect of a 25% glucose solution given via a soother with or without facilitated tucking with a similarly administered water placebo (control condition) on infant stress responses during and immediately after a tn-ECHO.

Secondary Objectives: To compare the performance time of a standard-defined tn-ECHO, the total number of times solutions are given, and the overall quality of the tn-ECHOs between treatment groups.

## **Hypotheses**

1. When given 25% glucose, soother and/or facilitated tucking during functional echocardiography, infants will show the lower behavioral stress scores than infants in the control groups.
2. When given 25% glucose, soother and/or facilitated tucking during functional echocardiography, the time taken by neonatologists to conduct the procedure will be less than for infants in the control groups.
3. The number of repeated application of the solution will be lower in the infants receiving the glucose solution.
4. The quality ratings of the tn-ECHOS will be higher in the group of infants who receive sucrose+soother/and or facilitated tucking).

## **Study Design**

Fatorial 4-arm, randomized double blind controlled study.

## **Inclusion Criteria**

Infants born between 26-42 weeks of gestational age admitted to the Neonatal Intensive Care Unit and Intermediate Nursery at Children's and Women's Health Centre of British Columbia (C&W) who are stable enough to have a tn-ECHO. To avoid bias in completing time of the tn-ECHO we have excluded purely educational studies.

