## **Methods**

Parents will be asked for written informed consent prior to randomization. It is not standard of practice to obtain parental consent for procedures like echocardiography that are clinically indicated; therefore, the consent will be purely for research purposes.

One hundred and four infants will be randomized to one of four intervention groups (Grp 1: glucose + soother; Grp 2 glucose + soother + facilitated tucking; Grp 3: water + soother; Grp 4: water + soother+facilitated tucking) which will take place during a single tn-ECHO examination, at the discession and after consultation with the medical team.

Randomization to each group will be determined by generating randomly permuted sequential blocks of four and six allocation numbers. The Clinical Services Research Unit will initiate the randomization process and provide the information regarding group allocation that will guide the intervention. Access to the randomization list will be through a web-based system that will enable online interactive checking of the inclusion/exclusion criteria before authorizing random allocation. This system is very reliable with 24-hour on-line support; as part of the data management services, a person will be available by phone during working hours at C&W to provide back-up for the system for unanticipated events. Randomization and preparation of the solutions will then be done by the pharmacist on site who will provide the solutions in unmarked syringes containing 5ml of either water or 25% glucose.

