## **Procedures**

All testing will take place in the NICU and Intermediate Nursery at C&W. As in our previous studies, five minutes before, during and five minutes after the tn-ECHO procedure, a close up image of each infant's face and upper extremities are videotaped. The digital, color camera is set up using a tripod. Using a foot pedal attached to the camera, recordings are synchronized to mark events. These tapes will be used to provide blinded behavioral coding of our primary outcome measure in conjunction with our bedside scoring described below.

For all groups, each infant will remain in his/her incubator/cot, positioned with rolls around the body to promote a flexed position. Every attempt will be made to have the procedure scheduled one hour post feed, if the infant is feeding. After a 20 minute rest period, five minutes before the contact of the physician to conduct the examination, an attending physician who is not conducting the tn-ECHO will assess the infant's baseline stress levels over a 30 second period using the Behavioral Indicators of Infant Pain (BIIP). BIIP score will then be measured 2 min after first administration of the solution (at time of starting of the tn-ECHO), then halfway through the assessment (as defined per echocardiographical images obtained, after completion of the right ventricular long axis view with RVO), and finally immediately after the last contact of the physician.

With respect to the glucose/water administration, two minutes before the first contact by the physician performing the tn-ECHO, each infant will be given either 0.5ml of 25% glucose (26-31 weeks gestational age group) or 1.0 ml of 25% glucose (32-42 weeks gestational age group). The solution will be applied to the anterior portion of the tongue followed by insertion of a soother. The soother will be held in the infant's mouth to ensure that continuous contact is maintained throughout the testing period. During the course of the assessment (estimated about 20 min), this application can be repeated if necessary (if the infant's movements interfere with the quality of picture obtained) to a maximum of four times, adding up to max 2ml of 25% glucose in the 27-31 weeks gestational age group or 4ml of 25% glucose in the 32-40 weeks gestational age group. During each tn-ECHO, infants have additional handling only if it is required to maintain physiological stability. Pharmaceutical interventions are an exclusion criterion for the study.

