## **Outcome Measures**

### *Primary Outcome Measure*

The primary outcome measure will include changes in BIIP scores across phases (Baseline, maximal score at first contact by physician, ½ through the tn-ECHO, Recovery) of the study. The Behavioral Indicators of Infant Pain (BIIP) is a reliable and valid scale we developed for assessing acute procedural pain in preterm infants, although it can also be used for measuring stress.

The BIIP combines into a single scale changes in sleep/wake states, five facial actions and two hand actions. The scoring sheet is appended. Scores range between 0-9, with scores 0-2 indicating mild or no pain/stress, 3-6 indicating moderate pain/stress and scores 7-9 indicating more severe pain/stress. In response to heel lance, under conditions where no intervention is provided, mean scores on the BIIP were  $5.3 \pm 2.6$  points. For less intrusive, but stressful procedures, such as diaper change, mean BIIP scores were  $3.1 \pm 0.5$ . To ensure reliability for

BIIP coding, physicians will be trained by [name] to achieve inter-rater reliability on the scale to above 0.85 (kappa). After the first 20 sessions, inter-rater reliability will be checked using the Bland and Altman approach which analyzes the differences in scores between two coders over the pair-wise mean of the two coders.

From the bedside videotapes, using the Noldus Observer system^16, one, 30-second block will be coded in real-time across four procedure phases:

|            |                                                                     |
|------------|---------------------------------------------------------------------|
| Baseline   | [T0] = 30 seconds, 5 minutes before first contact by the physician, |
| Time 1     | [T1] = 30 seconds beginning 2 minutes after first solution given,   |
| Time 2     | [T2] = 30 seconds after 4 and 5 chamber views finished              |
| Recovery 2 | [T3] = 30 seconds after the last contact by the physician           |

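### Allocation is not stratified by the gestational-age band that sets the solution volume, and adjustment for it depends on an imbalance being found: a modest, cheaply avoided loss of precision, not a bias

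*Protocol*

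**What the plan says.** Inclusion Criteria admits "Infants born between 26-42 weeks of gestational age admitted to the Neonatal Intensive Care Unit and Intermediate Nursery". Procedures divides these infants into two bands for the first application: "0.5ml of 25% glucose (26-31 weeks gestational age group) or 1.0 ml of 25% glucose (32-42 weeks gestational age group". The same paragraph then states the maximum total volume for differently bounded bands, 27-31 and 32-40 weeks.

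Methods randomises 104 infants to four arms. On the mechanism it says: "Randomization to each group will be determined by generating randomly permuted sequential blocks of four and six allocation numbers". No stratification factor is named. The web system checks eligibility before releasing an allocation.

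Statistical Analyses says that groups will be compared on demographic and medical information, and that differences found in these or in baseline BIIP will be entered as covariates. Other Data Collected lists gestational age at birth.

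On the outcome scale, Primary Outcome Measure calls the BIIP a "reliable and valid scale we developed for assessing acute procedural pain in preterm infants" and adds that it can also measure stress.

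**The concern.** The protocol itself treats gestational-age band as important enough to change the volume given. Band is also plausibly related to how strongly an infant reacts to handling. It is therefore a natural factor to balance, yet balance is left to chance with about 26 infants per arm.

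The only safeguard is an adjustment triggered by an observed difference. That rule has no stated threshold, and a moderate gap between arms of 26 may well not be called a difference. Which covariates enter the primary model is then decided after looking at the data. At stake are some precision in the primary contrast and the ease with which a reader accepts that the arms were alike in maturity. Stratification has to be in place before the first allocation and cannot be added afterwards.

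**Working it through.** **Inputs from the protocol.** 104 infants in four arms, so 104/4 = 26 per arm and 52 against 52 for glucose versus water (Methods). Two age bands (Procedures). Target difference 2 BIIP points, with 25 per group for 80% power (Sample Size Estimate).

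**Assumptions.** The protocol gives neither the share p of infants in the lower band nor the difference g between bands in BIIP change. I take p = 0.5, with 0.3 as a check, and g = 1 to 2 points.

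**The plan's own figure, as a yardstick.** The sample-size section states neither alpha nor SD. With two-sided alpha 0.05, 25 per group and 80% power imply SD = 2 / [√(2/25) × (1.960 + 0.842)] = 2.52. With SD 2.5 the standard error of a two-arm difference is 2.5 × √(2/25) = 0.71 points, and power by the normal approximation is 80.7%.

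**Chance gap in band share.** SD of the gap = √[2p(1−p)/n]; 95% range = ±1.96 × SD; mean absolute gap ≈ SD × √(2/π) = 0.798 × SD.

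| p | n per side | SD | 95% range | Mean absolute gap |
|---|---|---|---|---|
| 0.5 | 26 | 0.139 | ±0.27 | 0.11 |
| 0.5 | 52 | 0.098 | ±0.19 | 0.08 |
| 0.3 | 26 | 0.127 | ±0.25 | 0.10 |
| 0.3 | 52 | 0.090 | ±0.18 | 0.07 |

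The exact binomial chance of a gap of 15 points or more between two given arms of 26 is 33% at p = 0.5 and 29% at p = 0.3. The normal approximation gives 28% at p = 0.5, too low because it ignores that counts are whole numbers. In simulation, at least one of the six pairs of arms differs by 20 points or more in 34% (p = 0.3) to 42% (p = 0.5) of trials.

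**Shift in an unadjusted contrast** = gap × g.
- Two arms, typical: 0.11 × 1 to 0.11 × 2 = 0.11 to 0.22 points.
- Two arms, at the 95% limit: 0.27 × 1 to 0.27 × 2 = 0.27 to 0.54 points, or 14% to 27% of the 2-point target.
- Glucose versus water, typical: 0.08 to 0.16 points.

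The outcome is a change from baseline, so g must be a difference in *change*. A constant difference in BIIP level between bands cancels.

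**What fixing the band in the model gains.** Residual SD = √[2.5² − p(1−p)g²]. At p = 0.5:
- g = 1: √(6.25 − 0.25) = 2.45; power at 25 per group 82.3%.
- g = 2: √(6.25 − 1.00) = 2.29; power 87.0%.

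Both compare with 80.7% unadjusted.

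**Block sizes.** Six allocations over four arms give 6/4 = 1.5 per arm, so a block of six cannot be balanced. Stratifying without changing this would carry the problem into each band's list.

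**The case against.** The strongest reply is that simple unstratified randomisation is legitimate. Chance imbalance is already covered by the ordinary standard error, and the protocol collects gestational age and would adjust for a difference that is found. A typical shift of 0.1 to 0.2 points is small beside a standard error of about 0.7. All of this stands, and it rules out calling the design biased. What remains is that adjustment triggered by observed imbalance is weaker than a covariate fixed in advance, and that the better option costs almost nothing.

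A reader might infer stronger points that the document does not support.
- *That admitting term infants is an eligibility error, because the trial poses a preterm question.* The background starts from preterm infants, but the stated aim is whether the intervention "reduces stress and performance time during tn-ECHOs in infants in the NICU", the objectives and hypotheses refer to infants generally, and volumes are provided up to 42 weeks. The inclusion is deliberate.
- *That the BIIP is valid only in preterm infants.* The text describes it as valid "for assessing acute procedural pain in preterm infants" and does not say that it fails elsewhere. At most, the protocol states no support for its use in term infants. It also gives no age cut-off from which to define a subgroup in which the scale is valid.
- *That maturity and dose are two separate confounders.* The first volume is fixed by the band, so this is one variable. In the water arms the volume is not a glucose dose at all.

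**Conclusion.** The point holds as a modest design weakness. A factor that the protocol uses to set volume is neither balanced by allocation nor fixed in the analysis. With half the infants in the lower band, two arms would typically differ by about 11 percentage points in band share and could differ by 27. The resulting shift is typically about 0.1 to 0.2 BIIP points and at the extreme about 0.3 to 0.5, against a target of 2. These shifts rest on an assumed 1 to 2 point difference between bands in BIIP change, which the protocol neither states nor rules out; if there is no such difference, there is no shift. The loss is in precision and face validity. It gives no ground for calling the comparison biased or the eligibility range wrong.

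**What to change.** 1. Reconcile the age bands in Procedures: 26-31 and 32-42 weeks for the first application do not match 27-31 and 32-40 weeks for the maximum. Which limits apply is for the investigators to settle, but the bands cannot serve as strata until they agree.
2. Stratify the web randomisation by the two reconciled bands, with a separate permuted-block list for each and block sizes that are multiples of four.
3. Name the band, or gestational age at birth (already collected), as a covariate in the primary analysis whatever imbalance is seen, in place of selecting it by differences found.
4. Optionally, add a sentence on what supports using the BIIP in term infants.

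The cost is two lists in place of one, slightly less exact overall arm totals and one model degree of freedom. Eligibility, recruitment and sample size do not change.

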## **Exclusion Criteria**

Infants who have congenital anomalies, or a lethal condition in whom intensive care is not indicated; infants who have received analgesics or sedatives within 72 hours of the assessment; history of maternal abuse of controlled drugs and substances. Infants who are too unstable to be exposed to a tn-ECHO or who already have an ECHO performed by a Pediatric Cardiologist within 4 hours. Inability to obtain parental consent (due to language barrier, etc.).

## **Methods**

Parents will be asked for written informed consent prior to randomization. It is not standard of practice to obtain parental consent for procedures like echocardiography that are clinically indicated; therefore, the consent will be purely for research purposes.

One hundred and four infants will be randomized to one of four intervention groups (Grp 1: glucose + soother; Grp 2 glucose + soother + facilitated tucking; Grp 3: water + soother; Grp 4: water + soother+facilitated tucking) which will take place during a single tn-ECHO examination, at the discession and after consultation with the medical team.

Randomization to each group will be determined by generating randomly permuted sequential blocks of four and six allocation numbers. The Clinical Services Research Unit will initiate the randomization process and provide the information regarding group allocation that will guide the intervention. Access to the randomization list will be through a web-based system that will enable online interactive checking of the inclusion/exclusion criteria before authorizing random allocation. This system is very reliable with 24-hour on-line support; as part of the data management services, a person will be available by phone during working hours at C&W to provide back-up for the system for unanticipated events. Randomization and preparation of the solutions will then be done by the pharmacist on site who will provide the solutions in unmarked syringes containing 5ml of either water or 25% glucose.

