### **Sample Size Estimate**

In infant studies where self-report is not possible, a 2 point difference in pain scores has been considered clinically significant (10% reduction). Twenty five infants per group (100 total) will yield 80% power for a difference corresponding to the anticipated difference of 2 points on the

BIIP scale between treatment groups. Allowing for potential attrition of 10% and the need for including one or two co-variables in the analysis (e.g. differences in behavioral state at baseline), we may need to recruit up to 115 infants.

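### Permuted blocks of six do not divide over four arms, and with no rule for the two spare places the scheme does not guarantee the equal groups the sample size assumes

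*Protocol*

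**What the plan says.** The Study Design section describes a "Fatorial 4-arm, randomized double blind controlled study". The Methods section states "One hundred and four infants will be randomized to one of four intervention groups": glucose or water, each with a soother, and each with or without facilitated tucking. The same section says that randomisation to each group is determined by "generating randomly permuted sequential blocks of four and six allocation numbers".

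The Sample Size Estimate section then states that "Twenty five infants per group (100 total) will yield 80% power" for a 2-point difference on the Behavioral Indicators of Infant Pain (BIIP) scale. No unequal ratio appears anywhere in the protocol, and both stated totals split evenly: 100 = 4 × 25 and 104 = 4 × 26. Equal allocation is therefore inferred from the sample size and is not written as a ratio in Methods.

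The protocol does not say how a block of six is shared among four groups. Nor does it say that glucose and tucking are randomised from separate lists.

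**The concern.** A permuted block keeps *k* equally allocated arms in balance only if its length is a multiple of *k*. Four meets that condition for four arms and six does not. Blocks of four and six are a natural choice for two arms.

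This is not a detail left for another document. The protocol chose to fix the block sizes, and one of them does not fit its own design. Whoever programs the list has to invent a rule for the two spare places in every block of six, and arm sizes then depend on that unstated rule. A list built this way also cannot be checked against the protocol. The matter has to be settled before the list exists, because allocation cannot be redone once infants are enrolled.

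**Working it through.** **Inputs.** Arms: 4 (Study Design, Methods). Block sizes: 4 and 6 (Methods). Number randomised: 104 (Methods). Planned group size: 25, with 80% power for 2 points (Sample Size Estimate). The protocol gives neither the SD nor the significance level used, so 5% two-sided is assumed. The nearest SD in the protocol is 2.6, for heel lance without intervention (Outcome Measures).

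**1. The plan's own figure.** For two means, n per group = 2 × [(1.960 + 0.842) × SD / 2]².
- SD 2.5 gives 24.5, so 25 per group (power at 25: 80.7%; 79.1% by t test).
- SD 2.6 gives 26.5, so 27 per group (power at 25: 77.6%).
- Solving for the SD that gives exactly 80% at 25 per group: 2 / [(1.960 + 0.842) × √(2/25)] = 2.52.

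The stated 25 is consistent with an SD of about 2.5, but it cannot be confirmed because the SD is not stated. The value 2.52 is used below.

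**2. Divisibility.** 4 mod 4 = 0, so a block of four gives one place per arm. 6 mod 4 = 2 (6/4 = 1.5 per arm), so every complete block of six gives at least one arm more places than another. Balance can return over several blocks: two blocks of six with complementary spare places make 12, or 3 per arm. Nothing in the protocol requires that pairing.

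**3. Resulting imbalance at 104 infants.** Lists were simulated (at least 5,000 per scheme), with mixed block sizes taken as equally likely. That is an assumption, since the protocol gives no mix.

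| Scheme | Mean arm sizes | Largest minus smallest arm | Exactly 26 in each arm |
|---|---|---|---|
| Blocks 4 and 6, spare places to two different arms at random | 26 in each | mean 3.9; 97.5th percentile 7 | about 2% |
| Blocks 4 and 6, same two arms always over-filled | about 31, 31, 21, 21 | mean 10.8 | never |
| Blocks 4 and 8 | 26 in each | mean 0.5; never above 2 | about 74% |
| Simple randomisation, for reference | 26 in each | mean 10.4 | – |

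With random spare places, the smallest arm averages about 24 and the largest about 28.

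**4. Power.** Pairwise power = Φ(2 / [SD × √(1/n₁ + 1/n₂)] − 1.960), with SD 2.52 and before any attrition.
- 26 v 26: 81.6%.
- Random spare places, the two smallest arms: 79.6% on average (5th percentile 77.6%). Average loss: 81.6 − 79.6 = 2.0 points.
- Same two arms always over-filled: 31 v 21 gives 80.2%, and the two smallest arms average 72.5%. Loss for that pair: 81.6 − 72.5 = 9.1 points.

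**The case against.** Several points on the other side have force.

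**The scheme can be run.** A list can be produced once a fill rule is chosen, and with random or rotated spare places every arm still expects 26 infants. A reader might infer that the scheme *cannot* deliver equal groups, or that the sample size is invalid. Neither follows. The documents support only that equality is not guaranteed and that the rule is missing.

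**The imbalance is modest.** A range of about 4 is well below the 10.4 expected under simple randomisation, which is itself a valid method. Power depends on approximate arm sizes and not on exactly 26 in each. This stands, and it limits the weight of the point. A reader might also quote 31 v 21 as the expected result, but that requires the same two arms to be favoured every time, and the protocol says nothing of the kind.

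**Two factor-level lists.** The design is called factorial, the Statistical Analyses section speaks of a two-group analysis and main effects, and Methods has the research unit supply the allocation before the pharmacist randomises and prepares solutions. Blocks of four and six suit a two-level factor, and with one list per factor each margin would differ by at most 2 at 104 infants. This is possible, but Methods describes one allocation to four named groups. Two independent lists would also balance only the margins and not the four groups of 25. The objection does show that clarification might be enough.

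**Gestational age.** Because the solution volume differs by gestational-age band (Procedures), a reader might infer that failing to stratify by band is part of the same error. It is not. Chance imbalance in age is not bias, the Statistical Analyses section would include medical or demographic variables found to differ as covariates, and the Sample Size Estimate section allows for one or two of them. Stratification is a separate design preference and forms no part of this point.

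**Conclusion.** The point holds as a minor but real inconsistency. The block sizes in Methods do not fit four equally allocated arms, the rule for the spare places is missing, and so the equal groups in the Sample Size Estimate are assumed but not assured.

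Under the benign rule of random spare places, the consequence is arm sizes that typically differ by about 4 and a loss of about 2 percentage points of power in the least favourable pair. A loss of about 9 points arises only under a fixed over-filling rule that the protocol does not state. These figures rest on equally likely block sizes, an SD of about 2.5, a two-sided 5% level and 104 infants randomised. The divisibility conflict itself needs none of those assumptions. No bias is shown, and the sample size is not invalidated. The reason to act is that the list should be reproducible from the protocol and balanced as intended.

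**What to change.** Before the list is generated, amend the sentence in Methods so that block sizes are randomly mixed multiples of four, for example four and eight, and state the 1:1:1:1 ratio explicitly. With four and eight, about 74% of lists give exactly 26 per arm at 104 infants and the arms never differ by more than 2.

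If glucose and tucking are in fact randomised from separate two-level lists, blocks of four and six can stay. Methods should then say so, and should acknowledge that balance is controlled for each factor and not for the four groups.

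The cost is one protocol sentence and one setting in the randomisation program. The number of infants, the visits and the analysis do not change.
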